## Abstract

**Background:**

The onset of mental health problems generally occurs between the ages of 16 and 23 – the years in which young people follow post-secondary education, which is a major channel in our society to prepare for a career and enhance life goals. Several studies have shown that students with mental health problems have a higher chance of early school leaving. Supported Education services have been developed to support students with mental health problems to remain at school. The current project aims to study the effect of an individually tailored Supported Education intervention on remaining at school, study success, and satisfaction of students with mental health problems studying at an institute for intermediate vocational education and a university of applied sciences in the Netherlands.

**Methods/design:**

The design combines quantitative research (Randomized Controlled Trial; RCT) with qualitative research (monitoring, interviews, focus groups). One hundred students with mental health problems recruited from the two educational institutes will be randomly allocated to either the intervention or control condition. The students in the intervention condition receive the Supported Education intervention given by a Supported Education specialist, the students in the active control condition receive support as usual plus advice from a trained staff member on potential supportive resources regarding studying with mental health problems. The primary outcome ‘remaining at school’, and the secondary outcome ‘study success’ will be determined using data from the school’s administration. The secondary outcome ‘student satisfaction’ and other variables that will be studied in a more exploratory way, such as self-efficacy and study skills, will be determined through online questionnaires at baseline, at 6 and at 12 months follow-up. Focus groups and interviews with the students and Supported Education specialists will be carried out to complement the trial.

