### Sample size calculation

As mentioned before, this is the first RCT on the effect of our SEd intervention on remaining at school, our main outcome measure. Therefore, the effect size of our intervention on remaining at school is unknown. In such cases, it is a common convention to set the effect size at 0.5 [35], because a lower effect size would not be considered as clinically relevant [36, 37]. Therefore, we aim to demonstrate an effect size of 0.5 on the primary outcome measure remaining at school with a power of 80% and an alpha < 0.05.

Hence, for each condition 51 students are needed (total 102). Given an expected drop-out percentage of 25% from the study, 140 students (2 × 70) need to be included in the study. This is a feasible number, considering that 20–45% of students worldwide experience mental health problems [1, 38, 39].

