### Proposed analyses

Analyses will be performed according to the intention-to-treat principle and we will control for any variation in observable characteristics between conditions that remained after the minimization procedure that was used to randomize the students into the conditions. Missing values in the questionnaires will be prevented as the questionnaires are administered through an online secure software program (Enalyzer) in which answering to all items is obligated. The main outcome measure (remaining at school) will be insensitive for missing values as this data can be retrieved from the administration offices of the educational institutes. In case of missing data (for example, when a student does not fill in the second or third questionnaire), intention-to-treat analyses will be performed to account for incomplete outcome data [55]. In addition, it will be examined whether the rates of incomplete data differ between the control and experimental condition. To detect any outliers, the median absolute deviation method will be used [56]. Unrealistic outliers (due to e.g. data entry mistake) will be removed. In case of outliers with a realistic value, we will perform the analyses both with and without the outliers and we will report both results.

Descriptive statistics (e.g. frequencies, means and standard deviations) will be provided for all variables. Conventional statistical tests (e.g. regression, chi-square and ANOVA) will be used to address the research questions in accordance with how the data align with the assumptions of these tests (e.g. normality, homogeneity). In case the data are not normally distributed, the non-parametric equivalents will be used (e.g. the Friedman-test, the Mann-Whitney-test and the Wilcoxon signed-rank test).

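### The abstract randomises 100 students but the sample-size section requires 140; whether 100 keeps the stated 80% power depends on sidedness and on loss, so one target should be stated with its basis

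*Protocol article*

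**What the plan says.** The protocol article gives two numbers for the size of the trial.

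- Abstract, Methods/design: "One hundred students with mental health problems recruited from the two educational institutes will be randomly allocated".
- Sample size calculation: "for each condition 51 students are needed (total 102" evaluable, and then "140 students (2 × 70) need to be included in the study". The step between them is this: "Given an expected drop-out percentage of 25% from the study".

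The calculation is tied to the primary outcome: "we aim to demonstrate an effect size of 0.5 on the primary outcome measure remaining at school". The target is 80% power at an alpha of 0.05. The section does not say what kind of effect size 0.5 is, or whether the test is one- or two-sided.

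On completeness, Proposed analyses states: "The main outcome measure (remaining at school) will be insensitive for missing values", because the data come from the school administration. The Discussion repeats this for students who leave the study and describes the primary data as guaranteed. Study procedures adds that students consent to continued monitoring after leaving the study but may withdraw that permission.

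**The concern.** The abstract's figure counts students to be randomised, so it should equal the 140 of the sample-size section. It is 40 lower, and it cannot be the evaluable number either, because that is 102. Both figures are current text in the same article.

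The Discussion names low influx as a known bottleneck, sets a six-month inclusion period and plans a monthly check on recruitment. That check needs one target. If 100 were taken as sufficient, the margin for drop-out would be gone.

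A related point concerns the inflation. The calculation is for the primary outcome, yet it is enlarged for a loss that the article elsewhere says does not affect that outcome. The reader therefore cannot tell what power the primary analysis has at 140.

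**Working it through.** **Inputs.** Effect size 0.5, power 80%, alpha 0.05, 51 per arm, 25% drop-out and 140 included (Sample size calculation); 100 randomised (abstract); equal allocation (Study procedures). Assumption: 0.5 is a standardised difference *d* between two equal groups.

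**Step 1: reproduce 51 per arm.** Normal approximation: n per arm = 2(z_alpha + z_beta)²/d².

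- One-sided: 2(1.645 + 0.842)²/0.25 = 49.5, so 50. With the t-test: 50.15, so 51. This matches the protocol.
- Two-sided: 2(1.960 + 0.842)²/0.25 = 62.8, so 63. With the t-test: 63.77, so 64. This does not match.

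**Step 2: reproduce 140.** 51/(1 − 0.25) = 68 per arm, or 136 in total; the protocol rounds up to 2 × 70 = 140.

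**Step 3: power at each target.** Normal approximation: power = Φ(d√(n/2) − z_alpha). For 50 per arm, one-sided: Φ(2.500 − 1.645) = 80.4%. For 37.5 per arm, one-sided: Φ(2.165 − 1.645) = 69.9%. The t-test values are slightly lower:

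| Randomised | Analysed | One-sided | Two-sided |
|---|---|---|---|
| 100 | 100 (no loss) | 79.9% | 69.7% |
| 100 | 75 (25% lost) | 69.2% | 57.0% |
| 140 | 105 (25% lost) | 81.6% | 71.8% |
| 140 | 140 (no loss) | 90.3% | 83.6% |

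**Step 4: sensitivity to the effect scale.** The primary outcome is binary and the protocol gives no control-arm rate, so the range is shown under assumed control retention of 60% to 90%. Reading 0.5 as Cohen's h:

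- 100 analysed: 80% falling to 69% one-sided, 70% falling to 57% two-sided.
- 75 analysed: 69% falling to 58% one-sided, 57% falling to 45% two-sided.
- 140 analysed: 90% falling to 81% one-sided, 84% falling to 72% two-sided.

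At 60% retention this reading also gives 51 per arm one-sided (64 two-sided). Converting 0.5 to an odds ratio does not reproduce 51: it needs at least 74 per arm over the same range, and power is lower at every sample size.

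**The case against.** A reader might infer that 100 students simply cannot deliver the stated 80%. The document does not support that. The only basis that reproduces 51 per arm is one-sided, and there 100 fully analysed students give 79.9%, which is 80% for practical purposes. The protocol itself expects the primary outcome to be complete. The drop to about 70% with no loss comes almost entirely from moving to a two-sided test, not from having 100 instead of 102: two-sided, 51 per arm gives only 70.6%. Even the plan of 140 with 25% lost reaches only 72% on that basis. This objection stands, and the shortfall has to be stated conditionally.

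A reader might also infer that the 25% inflation contradicts the claim of complete primary data. That is too strong. Leaving the study and remaining traceable in school records can both be true, permission can be withdrawn, and student satisfaction is a questionnaire outcome that does need an allowance. Recruiting more than the primary outcome needs is conservative. What remains is narrower: the section does not say which analysis the allowance serves, or what power the primary analysis then has.

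Finally, the monthly recruitment check names no number and the abstract sets no stopping rule. That recruitment would end at 100 is a possibility, not something the article states. None of this reconciles 100 with 140.

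**Conclusion.** The inconsistency holds: 100 randomised in the abstract against 140 in the sample-size section, with no reconciling text. Where the 100 comes from is not stated.

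The consequence for power is conditional. On the protocol's apparent one-sided basis, 100 is adequate only if essentially nobody is lost from the analysis; with the stated 25% loss, power is about 69%. Two-sided, 100 gives about 70% at best and 57% after that loss. A target of 140 keeps at least 80% one-sided with or without the loss, and two-sided only if nearly all students are analysed.

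These figures rest on 0.5 as a standardised difference and on equal arms; for a binary outcome they also depend on the control-arm rate, as the sensitivity ranges show. Neither the missing sidedness nor the generic effect size is caused by the 100/140 mismatch, but the power at either target cannot be stated without settling them.

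**What to change.** 1. Use one number throughout. Change the abstract to 140, the only target with a derivation. If 100 is the real working target, say so in both places and restate the power with its sidedness and assumed loss: about 80% one-sided or 70% two-sided with no loss, 69% or 57% with 25% lost.
2. In Sample size calculation, give the power of the primary analysis when all randomised students are included from school records. At 140 and a standardised difference of 0.5 this is about 90% one-sided or 84% two-sided. Note that the 25% allowance mainly concerns the questionnaire outcomes.
3. Declare the sidedness and keep every figure on that basis. If it is two-sided, the 51 per arm must also change (63 to 64 per arm, 126 to 128 in total). Placing a two-sided power beside an unchanged 102 at 80% would mix two bases.

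Cost: text edits in the abstract and the sample-size section. If 140 is already the working target, recruitment, randomisation and data collection do not change.

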### Study procedures

We adhere to the SPIRIT 2013 guidelines [40], the checklist is provided in the Additional file 2.

Students who heard about the study through one of the recruitment strategies and are interested in participation, contact the research team by e-mail. A data coordinator will check the inclusion criteria and will then send a link to an online questionnaire which starts with information about the study and the question to fill out an informed consent form. In the informed consent (see Additional file 3), students state that they have been informed about the study and that they participate voluntarily. In addition, they give permission to collect grades and course credits from the school’s administration for the next five years, so we are able to follow the study success of the students after the current project has finished. They also give permission that in case they drop-out of the study, school progress keeps being monitored. Students have the right to withdraw this permission at any moment in time.

After signing the informed consent, the students fill out the baseline-questionnaire. Then, students will receive a student ID number and will be randomized, for both educational institutes separately, by the data coordinator in either the experimental condition (Supported Education-coaching; half of the group of students) or the control condition (support as usual plus advice on potential resources; half of the group of students), using the minimization approach [41] which aims to minimize imbalance between the conditions on specific factors, in our case on gender, age, ethnicity, study year, level of study, the number of credits completed, and level of psychological distress. The condition to which the student is allocated depends on the characteristics of the students that were already enrolled. Students will receive compensation (a gift coupon of 12,50 euro each) for filling in the questionnaires at baseline, 6- and 12-month follow-up. Within this 12-month follow up, each student experiences a critical moment in the educational pipeline: either transitioning to the next year or graduating. In Table 1, the Spirit flow diagram of the study procedure is presented.

**Table 1 Tab1:** SPIRIT flow diagram of the study procedure showing enrolment, interventions, and assessments

	Pre-intervention	Post-intervention (within one month)	6 month follow-up	12 month follow-up
**TIMEPOINT**	**t**_**0**_		***t***_***1***_	***t***_***2***_

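### The abstract gives 100 students to be randomised, while the sample-size section derives 102 needed and 140 to be included

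*Protocol article*

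**What the plan says.** The abstract, under Methods/design, states: "One hundred students with mental health problems recruited from the two educational institutes will be randomly allocated to either the intervention or control condition".

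The Sample size calculation section sets the goal: "we aim to demonstrate an effect size of 0.5 on the primary outcome measure remaining at school with a power of 80% and an alpha" of 0.05. It then says "for each condition 51 students are needed (total 102"), and next: "Given an expected drop-out percentage of 25% from the study, 140 students (2 × 70) need to be included in the study".

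Under Study procedures, a student is checked for eligibility, consents, completes the baseline questionnaire and is then randomised, half to each condition.

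Two further statements bear on the size of the problem. Proposed analyses says the primary outcome is taken from the schools' administration and should not suffer from missing values. The Discussion says this holds also for students who leave the study, because they consent to continued monitoring of their school progress. Study procedures adds that students may withdraw that permission at any time.

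The Discussion also promises a monthly check that recruitment is on track, without giving the number it is measured against.

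**The concern.** The number randomised is a core design figure, and the article states it in two ways that cannot both be right. Nothing in the text marks either as superseded or explains the difference. The abstract's 100 cannot be read as a rounded 102, because 102 is the number required after losses, whereas the abstract speaks of students allocated.

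Two things are at stake. First, the stated 80% power belongs to one of these numbers and not necessarily to the other. Second, if the trial closes at 100, a reader of the abstract would conclude that it met its target, and a reader of the sample-size section that it stopped 40 short.

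**Working it through.** **Inputs from the article.** Standardised effect d = 0.5, alpha 0.05, power 80%, 51 per arm, 25% drop-out, 140 to be included (Sample size calculation); 100 to be randomised (abstract); equal allocation (Study procedures). The article does not state whether the test is one- or two-sided.

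**Step 1: reproduce 51 per arm.** Normal approximation for two means, one-sided:

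n per arm = 2 × [(1.645 + 0.842) / 0.5]² ≈ 49.5, rounded up to 50.

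The corresponding t-test gives 50.15, rounded up to 51. This matches the plan. A two-sided test gives 63 (normal) or 64 (t-test) per arm and does not match. The one-sided t-test is therefore used below as the calculation that reproduces the plan's figure.

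**Step 2: reproduce 140.** 102 / (1 − 0.25) = 136, or 68 per arm. The stated 140 (70 per arm) is consistent with this, rounded up.

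**Step 3: compare the two figures.** 140 − 100 = 40, and 40 / 140 = 29% of the inclusion target. 102 − 100 = 2, so 100 is below the requirement even with no loss.

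**Step 4: power at each figure.** Normal approximation: power = Φ(0.5 × √(n/2) − 1.645), with n analysed per arm. For example, at n = 37.5, 0.5 × √18.75 = 2.165, and Φ(0.520) ≈ 0.699. The exact t-test values are alongside.

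| Randomised | Loss on primary outcome | Analysed per arm | Power, normal | Power, t-test |
|---|---|---|---|---|
| 100 | 25% | 37.5 | 69.9% | 69% |
| 100 | none | 50 | 80.4% | 79.9% |
| 140 | 25% | 52.5 | 82.0% | 81.6% |
| 140 | none | 70 | 90.5% | 90.3% |

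For reference, 51 analysed per arm gives 80.6% (t-test).

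**Step 5: what the figures represent.** They follow the plan's own standardised-effect calculation. The planned primary analysis is a logistic regression of a binary outcome. Reading 0.5 as Cohen's h for two proportions gives about the same requirement (49.5 per arm one-sided), so the comparison of 100 with 140 does not turn on that choice.

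**The case against.** The strongest reply accepts the mismatch but disputes its consequence. The primary outcome comes from school records, the analysis is by intention to treat, and the article says the outcome stays available after a student leaves the study. On those statements all 100 would be analysed, and power would be 79.9%, only 0.1 point below the goal. This stands. A reader might infer that the abstract's figure simply fails the 80% goal, but the article supports a material shortfall only if the sample-size section's own 25% drop-out is applied to the primary outcome. The article points both ways: that section applies the 25% to a calculation for exactly this outcome, while later sections say the outcome is complete. Because permission can be withdrawn, some loss between none and 25% is also possible.

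A reader might also point to the lower two-sided power at 100 (about 57% with 25% loss, 70% with none). Those values should not be charged to this discrepancy. Even 140 less 25% reaches only about 72% two-sided, because the 51 per arm is itself a one-sided number. That is a separate issue.

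Finally, a reader might infer that the article leaves the closing number open, or that the team is recruiting to 100. Neither is supported. The sample-size section derives 140, splits it by arm and calls it feasible. The 100 appears once, without derivation, and the monthly check names no number. What remains is that the abstract states a different randomised total and nothing reconciles it.

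**Conclusion.** The contradiction is certain and needs no assumption: 100 in the abstract against 140 in the sample-size section, for the same group of students. The sample-size section is the derived source, so the abstract is the more likely error, although the text does not settle this.

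The effect on power is conditional. Taking the one-sided t-test at d = 0.5 that reproduces 51 per arm, 100 randomised gives about 69% with 25% loss on the primary outcome and 79.9% with none. The corresponding values at 140 are 81.6% and 90.3%. Choosing 100 instead of 140 thus costs roughly 10 to 12 points on either assumption, but it takes the trial materially below 80% only where the drop-out applies.

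This should be corrected, because the planned number randomised is the figure against which recruitment and the stated power will later be judged.

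**What to change.** State one number to be randomised throughout.

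- If 140 is the target, change the abstract to 140. Nothing else in the sample-size section changes on account of this point.
- If 100 is the real target, replace 140 in the sample-size section, restate the power for 100, and say what loss is assumed for the primary outcome, in agreement with Proposed analyses and the Discussion.

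In either case, name the same figure as the reference for the monthly recruitment check.

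The cost is one sentence in the abstract, or a few in the sample-size section, plus the number in the recruitment check. Correcting the abstract to 140 adds no students to the derived target. Keeping 100 may mean stating a power below 80%, depending on the loss assumed.

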**Discussion:**

This RCT is the first to assess the effect of Supported Education on remaining at school, next to study success and student satisfaction among students with mental health problems. The use of a mixed-methods design will result in a thorough evaluation of the effect of the intervention. Issues regarding the influx and possible attrition of students in the follow-up are discussed.

**Trial registration:**

The study was registered with Trialregister.nl, no. NL8349, date registered: February 4th 2020. Register name: Community participation through education. Effectiveness of Supported Education for youth with mental health problems, a mixed methods study – Study protocol for a Randomized Controlled Trial.

Protocol Version: 3, date: May 28th, 2021.

**Supplementary Information:**

The online version contains supplementary material available at 10.1186/s12888-021-03329-5.

## Background

Over the past decade, an increase in mental health problems is seen among students in post-secondary education worldwide and these mental health problems are found to negatively influence the educational goals of these students [1–7]. For instance, having mental health problems increases the risk of dropping out of vocational and higher education up to twice as high [8–11]. For example, in the study of Hjorth et al. [9], the dropout rate amongst students with mental health problems was approximately 15% after five years, compared to a dropout rate of 8% in students without mental health problems. In an economy that requires (higher) education for upward occupational mobility, people who are unable to succeed in post-secondary/higher education or training may find themselves ultimately underemployed or unemployed [12–14]. Therefore, it is of the utmost importance to support students with mental health problems to complete their studies. Supported Education could be the support that is needed to reach that goal.

Supported Education (SEd) is defined as the provision of individualized, practical support and instruction to assist people with mental health problems to choose, get and keep their educational goals [15–18]. The mission of SEd is derived from the choose-get-keep model of the Boston Psychiatric Rehabilitation Approach (PRA): To help people with mental health problems develop the skills and supports required to be successful and satisfied in their chosen roles or environments [15, 19].

A SEd toolkit, based on this choose-get-keep model of psychiatric rehabilitation has already been developed to support students with mental health problems to return to or to remain at school. This toolkit provides tools and guidelines for organizations and professionals working with people with mental health problems [20]. In a small pilot project, the ‘keeping phase’ of the toolkit has been tested among eleven professionals and eleven students with mental health problems who follow post-secondary education [21]. The goal of the ‘keeping phase’ is to remain at school and increase study success and student satisfaction through the development of skills and support. The first results were positive: professionals indicated that the tools were useful, concrete and user-friendly; the students indicated that they felt more supported, got higher grades, and that their school functioning in general improved.

In the current project, we aim to test the effectiveness of the ‘keeping phase’ of the SEd toolkit more extensively and systematically using a randomized controlled trial (RCT) at an institute for intermediate vocational education and a university of applied sciences in the Netherlands. This RCT will be the first to assess the effect of the individualized SEd intervention on ‘remaining at school’ (primary outcome), next to indicators of study success and student satisfaction. These outcomes were chosen as remaining at school, and increasing study success and student satisfaction are the goals of SEd, and increasing the capacity of people to be successful and satisfied in the living, working, learning, and social environments of their choice is also the mission of PRA of which SEd is derived. Student satisfaction is strongly related to study success [22], and to involuntary dropout (i.e. students who were dismissed for failure to meet minimum academic standards) [23]. Furthermore, student satisfaction also influences students’ decision to continue with or drop out of school [24] even in students who were in good academic standing, but choose to dropout [23]. Examining whether the SEd intervention positively influences student satisfaction is therefore of high relevance. We are aware of only three RCTs on the effectiveness of SEd [25–27]. These studies differ from our RCT on several aspects: the type and contents of the intervention, the target group and the outcomes. Collins and colleagues [25] and Mowbray and colleagues [27] studied the effect of two *group* SEd interventions: a classroom intervention and a group model intervention that were more aimed at preparing for going to school, than at remaining at school. Collins and colleagues [25] found that students in the classroom model showed higher levels of empowerment and school self-efficacy than students in the control condition. Additionally, they found that the level of satisfaction with the program of the students receiving the group model intervention was significantly higher than of the students in the control condition. Mowbray and colleagues [27] only performed within-group analyses, so no conclusions can be drawn about the differences on the outcome variables between the experimental condition and the control condition. An RCT by Ellison and colleagues [26] was performed among *veterans* with post-traumatic stress disorder and showed that veterans in the SEd condition spent a greater amount of time on educational activities than the veterans in the control condition. In addition, several *pilot* studies on SEd have been performed (see for an overview of studies published between 1989 and 2009: [28], and for an overview of studies published between 2010 and 2020: Büttner S, Hofstra J, Farkas M, van der Velde J, Korevaar EL: Supported Education for students with mental health conditions: a systematic review of effectiveness studies from 2009-2020, submitted), showing positive effects on for instance educational status and level of employment [29, 30], study enrollment [31, 32], and Grade Point Average [29, 32]. However, the lack of a randomized controlled group in these studies limits the ability to draw strong conclusions. Although existing studies indicate that SEd may be an effective tool to support students with mental health problems, the outcome variables that were studied were very diverse and it remains to be determined whether SEd increases the chance that students remain at school, which is the ultimate goal of the keeping phase of SEd. If SEd is to become a viable alternative and widespread intervention and if mental health and education policies are to emphasize educational attainment, more effectiveness research on SEd models is critically needed [28, 33]. Therefore, in the current study we aim to examine the effect of SEd on remaining at school, next to study success and student satisfaction, using a mixed-methods design. The effect of SEd will be compared with the effect of an active control condition in which students will receive support as usual plus advice from a trained educational staff member on potential supportive resources. We chose for an active control condition to make sure that potential differences in effects of the intervention and control group cannot be attributed to general effects of receiving support, like getting attention from professionals, or being part of a group. Moreover, we thought it to be unethical to not support students who indicate that they are in a current need for support with their school functioning because of their mental health problems.

This design combines quantitative research (RCT) with a process evaluation through qualitative research (monitoring, interviews, focus groups). This process evaluation will be conducted to gain insight into the fidelity, reach, students’ experiences, experiences of the support staff of both the intervention and control condition, success- and fail factors, essential components of the SEd intervention according to students and SEd specialists and recommendations to further adapt the SEd intervention. As part of our examination of essential components of the SEd intervention, we will examine which of the five principles ([20, 34], Mullen MG, Nemec PB, Sullivan-Soydon AP, Thompson JL, Ellison ML, Sabella K, Stone B, Banko AL: Helping youth on the path to employment manual, unpublished; Sullivan-Soydon AP, Legere L: Supported Education operations manual, unpublished) of the choose-get-keep model of PRA [15, 19] on which the SEd intervention is based, are regarded as most helpful to achieve the students’ educational goals.

The principles of the choose-get-keep model of PRA are:
Self-determination: students make their own choices (setting their own educational goals) and accept responsibility for their educational process.Students are actively involved in their SEd process, determining the criteria for success and satisfaction, as well as in evaluating progress toward meeting their goals.Partnership between participant and SEd specialist.Development of participant skills and of environmental support/resourcesSupport as long as needed and wanted

To our knowledge, the importance of these principles according to the users of the SEd intervention has not been evaluated before.

